### Blood biomarker test

2.3

The blood draw will be conducted at median cubital vein at admission to hospital, 3 and 12 months. The blood biomarkers including fasting glucose, hemoglobin, cholesterol level, homocysteine, serum uric acid, high‐sensitivity C‐reactive protein, intercellular adhesion molecule 1, E‐selectin, matrix metallopeptidase 9, plasminogen activator inhibitor‐1, lipoprotein (a), interleukin‐6, interleukin‐18, macrophage chemoattractant protein‐1, oxidized low‐density lipoprotein, and lipoprotein‐associated phospholipase A2 will be tested.

### MR imaging

2.4

Baseline MR examination includes brain MR imaging and intracranial artery high‐resolution MR vessel wall imaging. All MR examinations will be performed on 3.0T Philips or Siemens MR scanners with 8‐channel phase‐array head coil or 16‐channel neurovascular coil. Brain MR imaging was conducted using a standard protocol including T1‐weighted (T1W), T2‐weighted (T2W), T2‐fluid‐attenuated inversion recovery (FLAIR), T2*‐weighted (T2*W), and diffusion‐weighted image (DWI) sequences. The imaging parameters are detailed in Table 1. The intracranial artery MR vessel wall imaging protocol includes three‐dimensional (3D) time‐of‐flight (TOF) MR angiography and pre‐ and post‐contrast T1 volumetric isotropic turbo spin echo acquisition (VISTA) at Philips MR platform or T1 sampling perfection with application‐optimized contrast using different flip angle evolutions (SPACE) sequence at Siemens MR platform. The 3D TOF imaging sequence was acquired with the following parameters: turbo field echo/fast low angle shot sequence, repetition time 25/21 ms, echo time 3.5/3.6 ms, field of view 180 × 180/173 × 199 mm³, matrix 300 × 300/384 × 301, and thickness 0.6 mm. The VISTA/SPACE imaging sequence was acquired using the following parameters: fast spin echo sequence, repetition time 800/900 ms, echo time 19/24 ms, field of view 200 × 181 × 45/158 × 158 × 158 mm³, matrix 332 × 300 × 150/256 × 256 × 246, and thickness 0.6 mm. The intracranial artery MR imaging parameters are presented in Table 2. The post‐contrast MR vessel wall imaging will be performed at baseline by intravenous administration of gadolinium contrast agent (Magnevist, Bayer Schering Pharma AG, Berlin, Germany) with the dose of 0.1 mmol/Kg. The recruited patients who were diagnosed with atherosclerosis in intracranial arteries by baseline MR vessel wall imaging will be eligible for 2‐year follow‐up study using MR imaging. The MR vessel wall imaging in the follow‐up study will be performed at the same MR platform to the baseline at 12 and 24 months by acquiring pre‐contrast T1‐VISTA or T1‐SPACE imaging sequence with the same imaging parameters to the baseline.

**Table 1 brb31154-tbl-0001:** Brain MR imaging parameters

	T1W	T2W	T2‐FLAIR	DWI
Sequence	FFE^a^/FISP^b^	TSE	TSE	EPI
TR, ms	233	3,000	7,000	2,858
TE, ms	4.6	80	140	92
FOV, mm³	230 × 183 × 133	230 × 183 × 133	230 × 230 × 133	230 × 230 × 133
Matrix	400 × 255	400 × 255	256 × 195	128 × 126
Thickness, mm	5.5	5.5	5.5	5.5
Scan time	1′58″	1′48″	1′52″	34″

FFE, fast field echo; FISP, fast imaging with steady‐state precession; TSE, turbo spin echo; EPI, echo planar imaging; TR, repetition time; TE, echo time; FOV, field of view.

^a^The imaging sequence is from Philips MR platform.^b^The imaging sequence is from Siemens MR platform; All the imaging orientations are transverse.

**Table 2 brb31154-tbl-0002:** Intracranial artery MR vessel wall imaging parameters

	3D TOF	T1‐VISTA^a^/SPACE^b^
Sequence	TFE^a^/FLASH^b^	TSE
TR, ms	25/21	800/900
TE, ms	3.5/3.6	19/24
Echo train length	‐	30/27
FOV, mm³	180 × 180/173 × 199	200 × 181 × 45/158 × 158 × 158
Matrix	300 × 300/384 × 301	332 × 300 × 150/256 × 256 × 246
Thickness, mm	0.6	0.6
Scan time	5′39″/6′	7′01″/8′06″
Orientation	Axial	Axial/Coronal

3D TOF, three‐dimensional time‐of‐flight; FOV, field of view; FLASH, fast low angle shot; FSE, fast spin echo; T1‐VISTA, T1 volumetric isotropic turbo spin echo acquisition; T1‐SPACE, T1 sampling perfection with application‐optimized contrast using different flip angle evolutions; TE, echo time; TFE, turbo field echo; TR, repetition time.

^a^The imaging sequence is from Philips MR platform.^b^The imaging sequence is from Siemens MR platform.


**Figure 2 brb31154-fig-0002:**
[figure not shown]
Work flow of the MR image analysis of intracranial artery using 3D‐CASCADE software. First step: outline of the center line of target segment of intracranial artery (a, M1 segment of middle cerebral artery); second step: automatic detection of the lumen and outer wall boundaries on the carved reconstructed image of target arterial segment (b); third step: manual adjustment of the lumen and outer wall boundaries on the axial image which is perpendicular to the center line (c)

**Table 3 brb31154-tbl-0003:** The imaging features of vascular diseases that lead to ICAS

	ICAD	Dissection	Arteritis	RCVS	MMD
Distribution	Any arteries	Any arteries (Intracranial: VA, BA)	The medium, small arteries of the meninges and cortex of the brain	Any arteries	Terminal ICA, Proximal MCA, Proximal ACA
Shape	Eccentric	Eccentric or combined	Concentric	Concentric	Concentric
Signal	Heterogenous	Hyperintensity (hematoma)	Homogenous	Homogenous	Homogenous
Enhancement	Dependent on vulnerability	Outer wall (±)	Diffuse enhancement	No or mild enhancement	Dependent on stage
Remodeling	Positive or negative	Unclear	Negative	Negative	Negative
Others	Intraplaque hemorrhage	Intimal flap, double lumen, aneurysmal dilatation	Exclusive diagnosis		Basal collaterals

ACA, anterior cerebral artery; BA, basilar artery; ICA, internal carotid artery; ICAS, intracranial artery stenosis; ICAD, intracranial atherosclerotic disease; MMD, moyamoya disease; MCA, middle cerebral artery; RCVS, reversible cerebral vasoconstriction syndrome; VA, vertebral artery.

### End points

2.6

The presence of progression of intracranial artery atherosclerotic plaques is the primary end point. The progression of intracranial plaque is defined when it meets any of the following criteria at 1‐ or 2‐year follow‐up compared with baseline measurements: (a) the maximum wall thickness increased ≥10% compared with baseline; (b) the stenosis increased by one or more grades on TOF MRA or MR vessel wall imaging; (c) occurrence of T1 hyperintensity within plaque; or (d) the enhancement increased by one or more grades on post‐contrast T1 VISTA/SPACE images. Secondary end points include new ischemic stroke or TIA at any vascular territories, or all‐cause death.

### Sample size estimation

2.7

According to previous studies, we assume about 20% of participants may have progression of intracranial atherosclerotic plaque in 2 years (Arenillas et al., 2008; Kwon et al., 2005; Ryu et al., 2014). Thus, 300 subjects are needed to estimate the progression rate of intracranial atherosclerotic plaque with a margin of error of 0.25× progression rate and a lost to follow‐up rate of 15%.

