**Methods:**

The ICASMAP study is a prospective, observational, and multicenter study by recruiting 300 subjects (18–80 years old) with recent stroke or TIA (within 2 weeks after onset of symptoms) in China. All the subjects will undergo MR imaging examination including brain and intracranial artery MR imaging at baseline. In addition, the clinical risk factors will be collected and blood biomarkers will be tested. A subgroup of more than 200 subjects who were diagnosed with ICAD according to baseline MR imaging will be followed up for 2 years. During the follow‐up study, MR imaging examination will be performed at 12 and 24 months. The primary end point is presence of progression of intracranial artery atherosclerotic plaques.

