### Study design and population

2.1

The ICASMAP study (NCT03417063) is a prospective, observational, and multicenter study. This study planned to recruit 300 patients (age range: 18–80 years old) who had recent ischemic stroke or transient ischemic attack (TIA; within 2 weeks after onset of symptoms) and ICAS (stenosis range from 30% to 99% that is the responsible lesion for symptoms) in at least one vascular bed determined by computed tomography angiography (CTA) or MR angiography. The ICAS lesions can be located in intracranial internal carotid artery, basilar artery, intracranial segment of vertebral artery (V4), M1 segment of middle cerebral artery, A1 segment of anterior cerebral artery, or P1 segment of posterior cerebral artery. The patients will be recruited from 18 different hospitals across Beijing–Tianjin–Hebei region in China. The exclusion criteria include the following: (a) severe carotid artery atherosclerotic disease (stenosis ≥ 70%); (b) cardiogenic thrombosis; (c) heart failure or respiratory failure; (d) renal dysfunction (serum creatinine ˃133 μmol/L); (e) serious disturbance of consciousness; (f) cerebral neoplasms; (g) intracranial hemorrhage; (h) claustrophobia; (i) contraindications to MRI; and (j) pregnant or plan to pregnant within recent 2 years. All subjects will undergo brain and intracranial artery MR imaging. For subjects who were diagnosed with ICAD (*n* > 200), the clinical follow‐up will be conducted at 3, 6, 12, and 24 months and the MR imaging follow‐up will be performed at 12 and 24 months, respectively. Previous studies reported that the progression rate of ICAS was 3.86% per year (Ryu et al., 2014) and the intra‐reader and inter‐scan variation in measuring maximum wall thickness of intracranial plaques was 6.67% (Zhang et al., 2018). Therefore, it might be reasonable to detect the 2 years’ progression of intracranial atherosclerosis disease (7.72%) which is greater than the variation of quantitative measurement by MRI. A flow chart of the study procedures is presented in Figure 1. The study protocol was approved by local Institutional Review Board, and all patients provide written informed consent.

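### Section 2.7 attaches the 0.25× margin to 300 recruits, but the calculation applies to ICAD patients entering MR follow-up, of whom the plan promises only more than 200

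*Protocol article*

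**What the plan says.** - Section 2.7 (Sample size estimation) sets the rate: "we assume about 20% of participants may have progression of intracranial atherosclerotic plaque in 2 years". It concludes that "300 subjects are needed to estimate the progression rate of intracranial atherosclerotic plaque with a margin of error of 0.25× progression rate", with a 15% allowance for loss to follow-up. That is the only allowance named.
- Section 2.1 (Study design and population) gives the same number as total enrolment: "This study planned to recruit 300 patients". These are patients with recent stroke or TIA and 30–99% intracranial stenosis, enrolled before the cause of the stenosis is known.
- The Abstract (Methods) limits who is followed: "A subgroup of more than 200 subjects who were diagnosed with ICAD according to baseline MR imaging will be followed up for 2 years". Section 2.1 repeats the figure as n > 200.
- Section 2.4 (MR imaging) makes follow-up imaging conditional on the baseline diagnosis: "The recruited patients who were diagnosed with atherosclerosis in intracranial arteries by baseline MR vessel wall imaging will be eligible for" the two-year follow-up.
- Section 2.6 (End points) makes plaque progression at one or two years against baseline the primary end point, so only followed ICAD patients can contribute to it.

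**The concern.** The number 300 has two meanings. In 2.7 it is the number of patients needed to estimate a progression rate. In 2.1 it is the number recruited with stenosis of any cause. Progression can be observed only in the ICAD subgroup, so recruits with dissection, arteritis, moyamoya disease or RCVS add nothing to that denominator. Section 2.7 allows for patients lost after entering follow-up but not for patients who never enter it.

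The margin in 2.7 is the only justification given for the study size, and it concerns the primary end point. If it was worked out for the wrong group, readers are told to expect a tighter progression estimate than the design can be relied on to give.

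**Working it through.** **Inputs**
- Progression rate p = 0.20 (2.7)
- Margin d = 0.25 × 0.20 = 0.05, or 5 points (2.7)
- Loss to follow-up 15% (2.7)
- Total recruitment 300 (2.1)
- ICAD subgroup followed: more than 200 (Abstract, 2.1)
- Confidence level: not stated for this margin. I assume two-sided 95%, the only level the article names (2.9, for the hazard ratio).

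**Step 1. Reproduce the 300.** For a single proportion, n = z²p(1−p)/d², then divide by 0.85.
- z = 1.96: 3.8416 × 0.16 / 0.0025 = 245.9, so 246 evaluable. 246/0.85 = 289.4, so 290 entering follow-up.
- z = 2: 4 × 0.16 / 0.0025 = 256 evaluable. 256/0.85 = 301.2, so 302 entering follow-up.

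The plan's 300 lies between these results. It is explained by about 95% confidence plus 15% loss, with essentially nothing left over for recruits who prove not to have ICAD.

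**Step 2. Precision by number of ICAD patients.** Evaluable N = 0.85 × ICAD patients. Half-width = 1.96 × √(0.16/N). Relative margin = half-width/0.20.

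| ICAD patients entering follow-up | Evaluable after 15% loss | Half-width (points) | Multiple of the rate |
|---|---|---|---|
| 300 (all recruits) | 255 | ±4.9 | 0.245× |
| 290 | 246 | ±5.0 | 0.25× |
| 270 | 229 | ±5.2 | 0.26× |
| 250 | 212 | ±5.4 | 0.27× |
| 241 (80.3% of 300) | 205 | ±5.5 | 0.27× |
| 200 (planned floor) | 170 | ±6.0 | 0.30× |

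The 80.3% share is the atherosclerosis share in the Chinese cohort described in the Discussion. Those patients were aged 18–45 with unilateral middle cerebral artery stenosis, so it only illustrates a share above the floor.

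With 200 ICAD patients and no loss at all, the half-width is 1.96 × √(0.16/200) = 5.5 points, or 0.277×. Perfect retention would therefore not recover 0.25× at the floor.

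**Step 3. ICAD share needed.** 290/300 = 96.7%, about 97%. The article gives no expected share, and its floor corresponds to 200/300 = 66.7%.

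**The case against.** **The figure of more than 200 is a floor.** This stands. A reader might infer that the rate will be estimated from about 170 patients, but the documents do not support that as a forecast. It is about the lowest number consistent with the plan, and more ICAD patients would give a narrower interval. Even so, at a 20% rate the margin is missed for any ICAD count below about 290.

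**A much worse shortfall might be inferred from the Discussion.** It cites a South Korean cohort in which 27.4% had atherosclerosis. Applied here, that gives about 82 ICAD patients (0.274 × 300), which conflicts with the plan's own n > 200. That cohort was also restricted to patients aged 55 or younger with at most one atherosclerosis risk factor and severe unilateral middle cerebral artery stenosis. ICASMAP recruits ages 18–80 across several arteries, and the Introduction says most intracranial stenosis is atherosclerotic. The scenario should not be used.

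**The confidence level is unstated and might be 90%.** At 90%, 174 evaluable and 205 entering follow-up would suffice, close to the planned floor. But 2.7 attaches the margin to 300, and 90% does not reproduce 300 from the inputs given. That reading would also need an unstated ICAD share of about 68% (205/300), so 2.7 would still need correcting.

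**The true rate may exceed 20%.** The earlier studies measured stenosis on angiography, whereas 2.6 counts any of four criteria. With 170 evaluable patients the relative margin is 0.26× at a 25% rate, and it reaches 0.25× at about 27%: 1.96 × √(0.27 × 0.73/170) = 0.067 = 0.247×. This is fair, so the shortfall holds at the plan's assumed 20% and not at every rate.

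**The quantity is descriptive.** This also stands. Section 2.7 contains no test, power claim or decision threshold, the mismatch does not bias the estimate, and the reported interval will show its own width.

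**Conclusion.** Section 2.7 is wrong as written. Its arithmetic is sound, but the result is the number of ICAD patients entering MR follow-up, and the design uses it as total recruitment of any etiology. The stated margin is met at a 20% rate only if about 97% of recruits have ICAD. That is not strictly impossible, but it is implausible in a study whose first primary objective is the distribution of etiologies, and the plan itself commits only to more than 200.

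The size is moderate: 0.30× at the floor and about 0.27× at an 80.3% share, against 0.25× stated, or about half a point to one point of extra half-width. This rests on 95% confidence, a 20% rate, 15% loss within the ICAD subgroup and the usual normal approximation. It should be fixed, but it does not undermine the study.

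**What to change.** Rewrite 2.7 so that the denominator is ICAD patients with evaluable follow-up MRI. State the confidence level. Replace the claim that 300 subjects give 0.25× with the precision delivered, for example: with at least 200 ICAD patients and 15% loss, about 170 or more will be evaluable; at a 20% progression rate the 95% confidence interval half-width is then at most about 6.0 points (0.30× the rate), and narrower if more recruits have ICAD.

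This costs wording only. No extra patients are needed, and the stated precision becomes slightly less favourable. If the sponsor prefers to keep 0.25×, about 290 ICAD patients must enter follow-up, and total recruitment must be raised by an explicitly assumed ICAD share (for illustration, 290/0.803 = 362 recruits). The correction does not require that.

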### Reproducibility

2.8

Fifteen subjects were randomly selected for reproducibility study. One reader interpreted the intracranial MR images twice with time interval of 2 months for minimizing the memory bias. The second reader interpreted the intracranial MR images blinded to the review results of the first reader. During reproducibility study, readers will measure lumen area, wall area, total vessel area, maximum wall thickness, stenosis, remodeling, T1 hyperintensity, and contrast enhancement at intracranial artery lesions.

### Statistical analysis plan

2.9

The continuous variables will be presented with mean ± standard deviation, and the categorical variables will be described as percentage. The prevalence of different vascular diseases, such as atherosclerosis, dissection, arteritis, moyamoya disease, and RCVS, that lead to ICAS in different age groups (<40, 40–50, 50–60, 60–70, and >70 years) will be calculated. The morphological measurements, T1 hyperintensity, enhancement patterns, and remodeling will be compared among different arterial diseases using One‐Way ANOVA or Mann–Whitney U test when appropriate. The progression rate of ICAD was calculated. Spearman correlation will be analyzed to determine the association of plaque features at baseline, clinical risk factors and blood biomarkers with progression of ICAD. Logistic regression model will be performed to calculate the odds ratio (OR) and corresponding confidence interval (CI) of plaque features at baseline, clinical risk factors and blood biomarkers in discriminating progression of ICAD before and after adjusting for confounding factors. Cox regression will be analyzed to calculate the hazard ratio and corresponding 95% CI of baseline intracranial artery vessel wall MR features in predicting for the cerebrovascular events. The intraclass correlation coefficient (ICC) and Kappa value were calculated for continuous and categorical variables in intra‐reader and inter‐reader reproducibility studies, respectively. All statistical analyses will be performed using SPSS 16.0 (SPSS Inc., Chicago, IL) and SAS (SAS Inc., North Carolina, NC).

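### With about 34 expected progressors, ordinary logistic fitting pushes adjusted odds ratios for real effects away from 1, more so in larger models; Firth fitting is a cheap improvement

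*Protocol article*

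**What the plan says.** The end of the Introduction makes risk factors for ICAD progression the secondary objective. Section 2.9 of the protocol article gives the method: "Logistic regression model will be performed to calculate the odds ratio (OR) and corresponding confidence interval (CI) of plaque features at baseline". The same sentence covers "plaque features at baseline, clinical risk factors and blood biomarkers in discriminating progression of ICAD before and after adjusting for confounding factors". No limit on model size is set, and no fitting method is named beyond logistic regression. SPSS 16.0 and SAS are the software.

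No number of events is stated, but it follows from other sections. Section 2.7 says "we assume about 20% of participants may have progression of intracranial atherosclerotic plaque in 2 years" and allows 15% loss to follow-up. The Abstract limits progression follow-up to "A subgroup of more than 200 subjects who were diagnosed with ICAD according to baseline MR imaging", and sections 2.1 and 2.4 agree that only patients diagnosed with ICAD are followed by imaging.

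**The concern.** A logistic model described without qualification is normally fitted by maximum likelihood. When events are few relative to the number of fitted terms, the maximum-likelihood log odds ratio of a factor with a real effect is biased away from zero. A harmful factor then looks more harmful, and a protective one more protective. The Introduction and Discussion cite factors of both kinds.

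The adjusted odds ratios are the main product of the secondary objective, and the Discussion expects them to inform the management of ICAD patients. Adjustment matters here because each added confounder increases the bias. The issue is the size of each estimate, not the number of tests.

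**Working it through.** **1. The plan's own sample size.** Section 2.7 has p = 0.20 and "with a margin of error of 0.25× progression rate", so d = 0.25 × 0.20 = 0.05. No confidence level is stated there; two-sided 95% is assumed. Then n = z²p(1−p)/d².
- z = 1.96: 3.8416 × 0.16 / 0.0025 = 245.9, so 246; 246/0.85 = 289.4, so 290.
- z = 2: 4 × 0.16 / 0.0025 = 256; 256/0.85 = 301.2, so 302.

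The stated 300 is therefore reproduced to rounding. It was set for the precision of one proportion, not for a regression model.

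**2. Expected progressors** = followed × (1 − 0.15) × 0.20.
- 200 followed: 170 evaluable, 34 progressors.
- 300 followed: 255 evaluable, 51 progressors. This needs every enrolled patient to have ICAD and be followed, so it is an upper limit.

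The design says more than 200, so 34 is the floor at these rates.

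**3. Possible model size.** The article lists about 36 candidates: 8 plaque measures (section 2.8), 12 clinical items (section 2.2) and 16 blood markers (section 2.3). How many enter one model is not given, so 5 to 20 terms are taken as an assumed range. Events per term are 34/5 = 6.8, 34/10 = 3.4, 34/15 = 2.3 and 34/20 = 1.7. With 51 events they are 10.2, 5.1, 3.4 and 2.6.

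**4. Bias of the log odds ratio.** Several simulations were run with true OR 2, 20% progression, correlated binary and continuous covariates, and 800 to 2,000 data sets per setting. They differ in the assumed covariate structure. Where reported, the Monte Carlo standard error is about 1.3 to 3.5 percentage points. The ranges below span the simulations. The last column is 2^(1 + bias) at 170 patients; for example, 2^1.12 = 2.17.

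| Terms | ML bias, 170 patients | ML bias, 255 patients | A true OR of 2 reads as (170) |
|---|---|---|---|
| 5–6 | 4–8% | 2–4% | 2.06–2.11 |
| 10 | 4–10% | 2–8% | 2.05–2.14 |
| 15 | 12–19% | 6–12% | 2.17–2.28 |
| 20 | 17–31% | 7.5–15% | 2.26–2.48 |

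Under Firth fitting the bias stayed within about 4% either way. For a factor with no effect (true OR 1, 10 covariates), maximum likelihood gave exp(mean log OR) = 0.99, so there was no shift.

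**5. Overall error (RMSE of the log odds ratio), 170 patients, ML to Firth.**
- 6 terms: 0.46 to 0.43 in one simulation, 0.49 to 0.45 in another.
- 10 terms: 0.53 to 0.46.
- 15 terms: 0.56 to 0.47, 0.57 to 0.47 and 0.60 to 0.49.
- 20 terms: 0.69 to 0.52.

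Wherever RMSE was compared, Firth's was the lower, including for null, protective and rare exposures.

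**The case against.** The article never says maximum likelihood, and it gives neither a covariate count nor a selection rule. A condensed article commonly leaves both to the full plan, so their absence is not an error. Nothing in section 2.9 says that all the listed factors enter one model; one exposure plus a few confounders fits the wording equally well. In such a model the bias is minor. In one of the simulations it was at most 4.3% of the log odds ratio for up to 10 covariates (2.00 becoming about 2.06), against a sampling SD of 0.34 to 0.48 and with interval coverage of 94–95%. The simulated sizes also vary about twofold with the assumed covariate structure.

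Most of this stands. It rules out treating the missing covariate list as a finding, and it makes the size conditional on model size. It does not remove the case for Firth. Maximum likelihood is the ordinary meaning of the method named, the article sets no cap that would keep models small, and Firth also lowered RMSE in models of about six terms.

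The event count is itself uncertain. If the 7.72% in section 2.1 were a two-year progression proportion, 170 to 255 evaluable patients would give only 13 to 20 events (170 × 0.0772 = 13.1; 255 × 0.0772 = 19.7). The any-of-four end point in section 2.6 could instead exceed 20%.

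**Conclusion.** The point holds as a modest one about a secondary objective. On the plan's figures about 34 progressors are expected from 200 followed patients, and at most 51. Under ordinary maximum likelihood, odds ratios for real effects would then be biased away from 1: slightly with 5–6 terms (4–8% of the log odds ratio at 170 patients), materially with 15 to 20 (12–31%), and by roughly half that or somewhat more at 255. This rests on the 20% rate, the 15% loss, maximum likelihood as the default reading, and assumed model sizes and covariate structures.

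A reader might infer three stronger claims that the documents do not support:
- **That the event count alone makes the adjusted odds ratios seriously inflated.** It does not; the number of terms decides, and the article does not give it.
- **That every odds ratio would be too large.** Null factors are not shifted on average, and protective ones would read too low.
- **That Firth fitting removes the problem entirely.** It largely removes bias on the log scale. In one simulation the arithmetic mean of the odds ratios under Firth was still 2.08 to 2.36 for a true value of 2, and the SD remained 0.33 to 0.52.

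**What to change.** Add one sentence to section 2.9: adjusted logistic models for ICAD progression will be fitted by Firth penalised likelihood, with profile-likelihood confidence intervals. SAS, already named there, provides this. If the full analysis plan already specifies it, nothing more is needed.

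The cost is one sentence and one software option, with no new patients, visits or data. Estimates become slightly less extreme. The change does not deal with testing many candidate factors, with choosing covariates from the data, or with the wide intervals that so few events will leave; these need their own handling.
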